### Participatory Co-Design Approaches to mHealth Intervention Development

Caregivers of detained adolescents have unique factors that require consideration when designing interventions and should be involved in the development process. Of note, caregivers often feel blamed for their child’s involvement in the system, internalize the stigma of being a “bad parent” [44], and feel overwhelmed by not understanding the court system and concerns for their child [44]. Further, they often harbor mistrust in the legal system, in part stemming from systemic racism [45] and a history of difficulty accessing effective community services and supports [46]. They are typically not included in or consulted regarding the development of interventions to help them, and as such, many existing interventions are not feasible or acceptable to them. Efforts to create relevant and accessible interventions must include their direct perspectives and buy-in to be successful.

Based upon principles of Community Partnered Participatory Research [47] and user-centered design [48,49], participatory informatics [50] is an approach to technology co-development that does not require technological expertise and includes users as equitable members in the design process. Involving caregivers in the design process increases the chances the mHealth intervention will be suitable for their needs, more satisfactory [49], and ultimately more effective at facilitating youth engagement in behavioral health treatment post release (via caregiver-level mechanisms of action; Figure 1).

### Study Objectives

This study will be the first to evaluate a mHealth intervention (RAISE app), designed through participatory co-design approaches with caregivers of detained adolescents, specifically focused on supporting caregivers of detained adolescents in managing their own stress while navigating the juvenile legal system. Using a randomized controlled trial (RCT) design, the primary goal of the study is to assess the feasibility, acceptability, and preliminary impact of the RAISE intervention on proximal caregiver outcomes (eg, parenting stress, parenting self-efficacy, and motivation for youth treatment) and more distal adolescent community-based treatment engagement outcomes.

#### RAISE App

The RAISE app was co-designed using participatory informatics approaches and the secure, web-based Chorus platform (Chorus Innovations, Inc) [51]. The Chorus platform provides a simple, visual, web interface to create interactive mHealth apps without requiring programming skills. Chorus includes interactive voice, texting, and mobile-based web app capabilities and is accessible from any device with internet browsing capabilities.

The co-design process is described in detail elsewhere ([name] et al, unpublished data). In brief, 6 caregivers of adolescents (12-18 years old) who had been detained in juvenile hall within the past year (including 50% currently detained) participated in 9 co-design sessions. Caregivers met either individually (n=2) or in pairs (n=4) with members of the research team to provide in-depth input regarding the needs of caregivers with detained adolescents, perspectives on acceptable intervention approaches (including reviewing mindfulness-based stress reduction approaches), and to develop and refine all RAISE app content. Once an initial version of the RAISE app was developed, co-designers and 6 new caregivers tested the app over a 3-month period and participated in 3 feedback sessions. The app was then refined in preparation for the current pilot trial.

The web-based RAISE app contains: (1) an 8-week stress-reduction intervention adapted from a mindful parenting curriculum [33]; (2) self-monitoring SMS text messages related to stress, mindfulness, and parenting self-efficacy (daily for the first 8 weeks, then reducing to 3 times per week for 3 weeks and weekly for the final 12 weeks); (3) weekly motivational SMS text messages, written by co-designers; and (4) resources related to navigating the juvenile legal system and accessing behavioral health treatment. Example pages within the RAISE app are displayed in Figure 2. The RAISE intervention is entirely self-guided, and the app can be accessed as frequently as a caregiver chooses; new content is released weekly for the 8-week stress-reduction intervention, with the option to revisit prior weeks’ material at any time. Each module contains mixed-media approaches to instruction, including audio-recorded exercises, videos (animated, with the exception of a yoga instruction video filmed by a live person), images, written text, and writing prompts to reflect on the content. The app will be “frozen” to changes during the trial (with the exception of addressing any unanticipated bugs), so all participants receive the same version of the intervention. During the informed consent appointment, users randomized to RAISE will set up an account with the assistance of a research assistant and be shown a tutorial video with key application features (which is also available in the app for their viewing at any time); no additional training is provided, however, if users experience technical difficulties with the application, they can contact the research team for support.

**Figure 2 figure2:**
[figure not shown]
Select pages of RAISE application.

#### Hypotheses

We hypothesize that caregivers receiving the RAISE intervention will experience reductions in their parenting stress and that their adolescents will be more likely to initiate behavioral health services post release. We will explore hypothesized mechanisms of intervention impact (eg, mindful parenting, parenting self-efficacy, and motivation for youth treatment) as well as potential moderators (eg, gender, race, and ethnicity).

## Methods

### Study Design

Caregivers of detained adolescents (N=60) will participate in the RCT to assess the preliminary impact of the RAISE intervention on caregiver stress and adolescent behavioral health services use post release. A study flow diagram is displayed in Figure 3. Caregivers of adolescents (12-17 years old) in placements mandated by the juvenile legal system will be enrolled in the study and randomized to either the RAISE intervention or to receive an informational brochure (comparison). Enrolled caregivers will complete a computerized set of questionnaires (on a tablet device, mobile phone, PC, or laptop computer) at baseline and 3- and 6-month follow-ups. The trial has been registered with ClinicalTrials.gov (NCT05032742) (Multimedia Appendices 1 and 2).

**Figure 3 figure3:**
[figure not shown]
Study flow diagram.

### Study Sample Size Determination

The main overall study focus is on the feasibility and acceptability of the codevelopment process and RAISE intervention; however, we will examine the direction of effects through this pilot RCT and cautiously consider effect size to inform sample size determination for a subsequent phase 2 efficacy trial. As with most pilot studies, these analyses are underpowered (for primary analyses considering a sample of 60 participants with α=.05, 4 of predictors, and estimating a medium effect size (Cohen f^2^=.15), power=.62). There are notable concerns with calculating effect sizes based upon pilot studies, including potential for overestimating and underestimating effects [52]. Given that we anticipate small to medium effect sizes, we followed published guidance to determine a planned enrollment of 30 participants per study arm [53].

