#### Statistical Analysis

##### Quantitative Analysis

Analyses will be conducted using IBM SPSS Statistics software. Descriptive statistics will be used to examine issues related to recruitment (eg, sufficient numbers of caregivers consenting and pace of recruitment), randomization (eg, whether participants are willing to be randomized), assessment (eg, valid, reliable, acceptable, and complete), and retention (eg, rates of follow-up assessment completion). Preliminary analyses will examine whether the randomization process was successful, comparing groups on multiple background (gender, race, etc) and baseline (parenting stress, caregiver mental health, etc) variables through independent samples *t* tests (continuous variables) and chi-square analyses (categorical variables). If there are group differences, subsequent analyses will be run both with and without accounting for these variables. Efforts will be made at each stage of analysis to assess the importance of race and gender. Initially, means, distributions, and reliabilities for all major measures will be examined separately by race and gender. Any observed differences across demographic subgroups will be considered in the interpretation of substantive analyses. The proportion of missing data will be examined before outcome analyses to determine whether a complete case analysis is appropriate or whether multiple imputation is warranted (eg, if there is a large proportion of missing data, ie, >5%; if there are patterns in missingness based on demographic factors) [64].

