#### RAISE Effectiveness

Outcome analyses will focus on proximal caregiver-level outcomes, including mindful parenting, parenting stress, parenting self-efficacy, perceived barriers to youth treatment, and motivation for youth treatment. Secondary distal outcomes will include adolescent treatment initiation and retention. Linear regression will be used for continuous outcomes (ie, mindful parenting, parenting stress, perceived barriers to youth treatment, motivation for youth treatment), logistic regression for 3- and 6-month follow-up dichotomous outcomes (ie, treatment initiation and adherence to mandated treatment), and Poisson or negative binomial regressions for count outcomes (ie, number of treatment sessions attended). All analyses will include the intervention group as a predictor and control for baseline level of the outcome variable, application usage, and demographic characteristics (determined during preliminary analysis). Potential moderators and mediators of intervention effects will be explored using the PROCESS macro in SPSS, which uses a regression framework. Moderation analyses will involve computing interaction terms of intervention group (intervention vs comparison) by key demographic factors (eg, caregiver age, gender, race, mental health, substance use, and youth age, centered before computing interaction term for continuous variables). Mediational effects will examine the impact of intervention group on key proximal outcomes assessed at 3 months (ie, mindful parenting, parenting stress, parenting self-efficacy, perceived barriers to youth treatment, and motivation for youth treatment) and their impact on distal youth treatment engagement and retention outcomes assessed at 6 months. An “Intent to Treat” design, where all initially assigned to the intervention group are included in analyses, whether or not they used the intervention, will be used.

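### The stated power of .62 belongs to a joint test of all four predictors, not to the single group coefficient that measures the RAISE effect

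*Protocol article*

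**What the plan says.** Study Sample Size Determination describes the trial as a pilot focused mainly on feasibility and acceptability and calls its analyses underpowered. In support it gives one calculation, "for primary analyses considering a sample of 60 participants with α=.05, 4 of predictors, and estimating a medium effect size", and completes it as "estimating a medium effect size (Cohen f^2^=.15), power=.62". It does not say whether f² refers to the whole model or to the group term, or how many of the four predictors are tested.

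The same section bases the sample size on something else: "Given that we anticipate small to medium effect sizes, we followed published guidance to determine a planned enrollment of 30 participants per study arm".

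The Hypotheses section expects RAISE to reduce parenting stress. RAISE Effectiveness specifies linear regression for continuous outcomes and states: "All analyses will include the intervention group as a predictor". The remaining terms (baseline outcome, application usage, demographic characteristics) are controls. No section plans a joint test of all predictors.

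**The concern.** A power figure attached to the primary analyses should describe the test that answers the primary question. Here that is a 1-df test of the group coefficient. An overall test of the model answers a different question, namely whether anything in the model predicts the outcome. Baseline stress alone can make that true.

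The article says effect sizes from this pilot will inform a later efficacy trial, and .62 is its only numerical statement of what the design can detect. A reader who takes it as the chance of detecting a medium RAISE effect is misinformed. A planner who repeats the same calculation would size the next trial for the wrong test.

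**Working it through.** **Inputs from the article.** N=60, allocated 1:1 (Randomization); α=.05, 4 predictors, f²=.15, stated power .62 (Study Sample Size Determination); group as one predictor in a linear regression (RAISE Effectiveness).

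**Inputs assumed.** Any correlation r between baseline and follow-up, any attrition, and any distribution of app use. The article gives none of these.

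**Formula.** λ = f²·N = 0.15 × 60 = 9.0. Denominator df = 60 − 4 − 1 = 55. Power is the probability that a noncentral F with (u, 55) df and noncentrality λ exceeds the central 5% critical value, where u is the number of coefficients tested.

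**Step 1: reproduce .62.**

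| Coefficients tested, u | Power at f²=.15 |
|---|---|
| 4 (whole model) | 0.621 |
| 3 | 0.677 |
| 2 | 0.746 |
| 1 (group only) | 0.838 |

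In the stated four-predictor model, only the joint test of all four matches .62. A 4-df test inside a five-predictor model also gives 0.620, but that is still not the group coefficient.

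**Step 2: what the joint test can detect without RAISE.** Suppose the group effect is exactly zero and only baseline stress predicts follow-up. Then model f² = r²/(1 − r²). At r=0.36, f² = 0.1296/0.8704 = 0.149 and the joint test has power .62. At r=0.6, f² = 0.36/0.64 = 0.5625 and power exceeds .99.

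**Step 3: power for the group coefficient.** For a 1:1 group term uncorrelated with the other covariates, partial f² = d²/4 with d in residual SD units, so d = 2√f². If d is in raw SD units and baseline correlates r with follow-up, f² = (d²/4)/(1 − r²).

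| Assumed RAISE effect | Partial f² | Power, u=1, N=60 |
|---|---|---|
| f²=.15, so d = 2√.15 = 0.77 | .15 | 0.84 |
| d=0.5, r=0.6 (assumed) | .0625/.64 = .0977 | 0.66 |
| d=0.5, no gain from baseline | .0625 | 0.48 |
| f²=.02, so d = 0.28 | .02 | 0.19 |

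With r from .5 to .7, the d=0.5 figure runs from 0.59 to 0.76. The 1-df test has power .62 only at f² of about .089 (d about 0.60), a value the article does not state.

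**Step 4: matching precision at N=60.** Half-width = t(.975, 55) × √(1 − r²) × √(2/30), with t = 2.004 and √(2/30) = 0.258. With r=0 this is 0.52 raw SD. With r=0.6 it is 2.004 × 0.8 × 0.258 = 0.41 raw SD.

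**Step 5: application usage.** Step 3 takes group as uncorrelated with the other covariates. RAISE Effectiveness also adjusts for application usage, and the brochure arm has no app. If usage is zero in that arm and has coefficient of variation c in the RAISE arm, the squared correlation of usage with group is 1/(1 + 2c²) and the variance inflation is 1 + 1/(2c²). That is 3 at c=0.5 and 1.5 at c=1 (both assumed). Dividing f²=.0977 by these values gives .0326 and .0651, so for the same coefficient and residual variance the 0.66 falls to 0.28 and 0.49.

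**The case against.** The strongest reply is that the figure decides nothing. The 30 per arm come from published guidance, the .62 is a parenthesis illustrating that the pilot is underpowered, and the section already warns against reading much into pilot effect sizes. This stands. A reader might infer that N=60 rests on a faulty calculation and is invalid; the article does not support that.

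A reader might also infer an arithmetic slip. There is none: .62 is correct for the joint test. The fault is that it is presented as the power of the primary analyses. The article does not name the test used, so the identification rests on reproducing the number. The ambiguity does not rescue the figure: read as whole-model, f²=.15 gives .62 for a test nobody plans; read as the partial group effect, it gives 0.84.

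A third tempting reading is that .62 ignores dropout. The article states no attrition rate, and its 5% missing-data threshold only guides the choice of multiple imputation; it predicts no loss. A condensed article may leave attrition to the full protocol. Attrition is therefore not part of this point.

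Finally, a corrected figure that ignores application usage would also not describe the model as written. That is right, and the fix has to say so.

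**Conclusion.** The point holds as a misdescribed power figure. The stated .62 is the power of the joint 4-df test (0.621), and no section plans that test. For the group coefficient the power is 0.84 at f²=.15, 0.66 or 0.48 at d=0.5 with or without an assumed baseline correlation of 0.6, and 0.19 at f²=.02. These values rest on N=60 analysed, four predictors, linear regression, and group uncorrelated with the other covariates.

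The error has no fixed direction, so it would be wrong to say that .62 simply overstates power. It is too low if RAISE has a partial f² of .15 and too high for smaller effects such as d=0.5 without baseline gain. The article writes "Given that we anticipate small to medium effect sizes", and an effect of d about 0.77 sits poorly with that. Over the d=0.5 and f²=.02 rows the design remains underpowered, so the article's qualitative conclusion survives and only its number does not.

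**What to change.** Keep N=60. Replace the .62 with power, or the expected 95% CI half-width, for the 1-df group coefficient at a stated d or partial f². Compute power and half-width for the same N and the same baseline correlation, and label every value not taken from data as an assumption. A consistent statement would be:

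*With 60 caregivers analysed, four predictors, two-sided α=.05 and a group difference of d=0.5 in raw SD units, power for the group coefficient is about .48 with an expected 95% CI half-width of about 0.52 SD if baseline adds no precision, and about .66 and 0.41 SD if baseline and follow-up correlate 0.6 (assumed). These figures apply to a model without application usage, which is structurally tied to group and would lower power further.*

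If a loss scenario is wanted, label it as assumed and change both figures together. With 20% loss (N=48, 43 df) and r=0.6, power is about .56 and the half-width is 2.017 × 0.8 × √(2/24) = 0.47 SD.

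The cost is one rewritten sentence. Sample size, allocation, data collection and conduct do not change.

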### Intervention Condition (RAISE)

Caregivers (n=30) who are randomized to the RAISE intervention will receive access to the web application for a 6-month period. The first 3 months are considered the main intervention window, as this is the timeframe when the 8-week stress reduction intervention content is intended to be completed. Caregivers have the option to revisit this material at any time during the 6-month access period, and use of all RAISE app features is captured in app logs. Caregivers can access the web application on any device with an internet browser and log in using a unique username and password. RAISE is provided at no cost to participants.

### Informational Brochure Condition (Comparison)

Caregivers (n=30) who are randomized to the comparison condition will receive an informational brochure about the juvenile legal system. Content for the brochure was adapted from existing guides distributed to caregivers by local jurisdictions in partnership with juvenile legal system professionals [54].

### Recruitment

Enrollment for the trial commenced in October 2023 and is anticipated to conclude by April 2025. Caregivers are recruited through passive and active techniques. Flyers and business cards with a QR code, which when scanned directs to an online eligibility survey and video explaining the study, are posted in public places (detention center waiting areas, court buildings, etc) and distributed electronically by legal system partners (probation officers, attorneys, behavioral health clinicians, etc). Study staff also recruit caregivers through active means, specifically by talking directly with families during family visitation in detention centers. Caregivers who provide their contact information and permission to be contacted by the study team are offered an opportunity to learn more about the study by meeting with a research assistant either remotely via Zoom or in person. Caregivers who are eligible and interested in participating complete an informed consent discussion with a research assistant and the baseline assessment before randomization (Multimedia Appendix 3).

### Inclusion and Exclusion Criteria

Eligible caregivers must be the parent or legal guardian of an adolescent who (1) is currently detained by the juvenile legal system, (2) is 12-17 years old, (3) has an identified substance use or substance use and co-occurring mental health need, and (4) will ultimately be released into the community to the care of the enrolled caregiver. Computer or internet literacy is not an inclusion criterion for the study. Given that adolescents within this population are not always raised or cared for by their biological parents, we use the term “caregiver” to define the adult who has principal responsibility for the raising and care of the adolescent, and who can provide legal consent and enrollment in services and research studies. In addition, detention by the juvenile legal system can include secure facilities such as juvenile detention centers or alternative placements such as group homes, which are less secure, but where youth are not technically allowed to leave freely.

### Randomization

Participants will be randomized (using the REDCap [Vanderbilt University] randomization module [55,56]) to either the RAISE intervention group (30/60, 50%) or the informational brochure comparison group (30/60, 50%) directly after consent and completion of the baseline assessment. Randomization is blocked (to avoid “runs” of assignment to the same condition) and stratified by gender to ensure balance between the 2 conditions (because most caregivers are anticipated to identify as women). The randomization table is generated by a biostatistician and is not visible to the research assistant before assignment; no blinding was used. Participants will not be told which condition is the intervention of interest, but during the informed consent discussion are informed that they may be invited to test a mobile app.

### Ethical Considerations

This study was approved by the Institutional Review Board at the University of California, San Francisco (#20-32010) and certified by the Office for Human Research Protections. Caregivers will provide informed consent before completion of their baseline assessment during an appointment with a research assistant. Study data do not contain personally identifiable information and are coded with a unique study identification number; a list linking study identification numbers to specific participants is securely maintained and only accessible to trained study staff. Each participant will be offered a US $40 gift card as compensation for their time for each survey or interview completed (total possible compensation: US $160). A Data Safety and Monitoring Board was formed before the initiation of the RCT and includes 4 members with expertise in clinical trials, mental health research with underserved populations, and research with youth and families. Adverse events will be reported and managed in accordance with the institutional review board and the funder’s requirements.

